#### Outcome measures

A suite of outcome measures recommended and previously used in research for this patient group will be used [7,9,13]. A summary of these outcome measures and the tool used are detailed in Table 2.

**Table 2 T2:** Outcome measurement tools

**Outcome**	**Assessment**
Function	Patient rated wrist evaluation*
Disability	Disabilities of the arm, shoulder and hand
Health-related quality of life	EQ-5D-3 L (Australian)
Pain	Visual analogue scale
Satisfaction	Visual analogue scale
Grip strength	Jamar dynamometer
Range of movement	Goniometric evaluation
Radiological outcomes	Study specific generated checklist
Adverse events	Study specific generated checklist

*Primary outcome measure.

Patient demographic information and baseline (pre-injury) functional status will be collected after consent to take part in the trial. Structured information regarding other injuries which may affect outcome e.g. disruption of the carpal ligaments, will be collected but all patients will be included in the analysis.

The primary outcome measure for this study is the:

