## Abstract

**Background:**

Distal radius fractures are among the most common fractures seen in the hospital emergency department. Of these, over 40% are considered unstable and require some form of fixation. In recent years with the advent of low profile plating, open reduction and internal fixation (ORIF) using volar plates has become the surgical treatment of choice in many hospitals. However, it is currently unknown which plating system has the lowest complication rate and/or superior clinical and radiological outcomes following surgery. Few studies have compared different types of plates, which may have various features, different plate and screw designs or may be manufactured from different materials (for example, stainless steel or titanium). This study will specifically investigate and compare the clinical and radiological outcomes and complication rates of two commonly used volar plating systems for fixation of distal radius fractures: one made from stainless steel (Trimed™ Volar Plate, Trimed™, California, USA) and the other made from titanium (Medartis® Aptus Volar Plate, Medartis®, Basel, Switzerland). The primary aim of this study is to determine if there is a difference on the Patient Reported Wrist Evaluation six months following ORIF using a volar plate for adult patients with a distal radius fracture.

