### EQ-5D (Euroqol-5D)

The EQ-5D-3 L is a validated, generalized, quality of life questionnaire consisting of 5 domains related to daily activities with a three-level answer possibility. The EQ-5D-3 L obtains information pertaining to the current health status of the participant and measures physical, emotional and social status. The combination of answers leads to a total quality of life score.

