### Radiographic evaluation

Standard posterior-anterior, lateral and oblique radiograph projection views will be taken to confirm diagnosis pre-operatively. X-rays will then be routinely performed as per the standard level of care to assess for union, standard radiographic parameters and hardware complications. An additional x-ray will also be taken at 24 months post-operation to assess for malunion, radiographic parameters and hardware complications.

These outcomes will be administered by a blinded assessor at the timeframes detailed in Table 3:

**Table 3 T3:** Intervals for outcome measures

**Assessment**	**Baseline**	**2 weeks**	**6 weeks**	**3 months**	**6 months**	**1 year**	**2 years**
**PRWE**			X	X	X	X	X
**Patient satisfaction**			X	X	X	X	X
**Pain**		X	X	X	X	X	X
**Radiological outcomes**	X	X	X	*	*	*	X
**AROM**		X	X	X	X	X	X
**Complications**		X	X	X	X	X	X
**EQ5D**	X		X	X	X	X	X
**Quick DASH**			X	X	X	X	X
**Grip strength**				X	X	X	X

*Only if required as part of treatment/normal care.

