#### Sample size

Recruitment of a total of 130 participants (65 in each group) is anticipated to take approximately 104 weeks (assuming a 75% recruitment rate of eligible participants) based on historical emergency department presentation rate of this patient group. After allowing for a 30% loss to follow up, this investigation has 95% power to detect a between group mean difference in the primary outcome function (PRWE) of 10 (SD-15).

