#### Statistical analysis

Baseline demographic and clinical data will be reported using descriptive statistics and tabulated (e.g. Students *t*-test for continuous variables and Pearson chi-square for categorical variables). Between group differences in baseline data will be examined using unpaired conventional tests of hypothesis (such as unpaired t-tests) depending on the nature of the data. Between group and within group differences in outcome measures over time will be examined using a priori unpaired and paired conventional tests of hypothesis (such as Analysis of Variance with simple effects examined using t-tests) depending on the nature of the data. Bonferroni adjustments for multiple comparisons will be made where appropriate to mitigate risk of type-1 error. The complication rates will be reported in terms of frequency. The frequencies of complications will be compared using statistical analysis such as the Pearson chi-square statistic. For missing data values at different time points, a mixed linear regression model for repeated measures will be performed. Subanalysis for age will be undertaken to account for patients with osteoperotic bone.

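### The promised pre-injury functional status has no named instrument and no place in Table 3, so the primary PRWE has no pre-randomisation value for a balance check or for adjustment

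*Protocol article*

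**What the plan says.** Under Outcome measures, the article says "Patient demographic information and baseline (pre-injury) functional status will be collected after consent to take part in the trial". It does not say by which instrument. In the same section, Table 2 pairs function with the "Patient rated wrist evaluation" and flags that as the primary outcome measure; disability is paired with the DASH.

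The schedule is introduced under Radiographic evaluation: "These outcomes will be administered by a blinded assessor at the timeframes detailed in Table 3". Table 3 has a baseline column, in which two of the nine rows are marked: radiological outcomes and EQ-5D. PRWE and QuickDASH are first marked at 6 weeks.

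The abstract gives the primary aim as to "determine if there is a difference on the Patient Reported Wrist Evaluation six months following ORIF". Under Statistical analysis, the article plans that "Between group differences in baseline data will be examined using unpaired conventional tests of hypothesis", and for follow-up that "Between group and within group differences in outcome measures over time will be examined using a priori unpaired and paired conventional tests of hypothesis". It names no baseline covariate.

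**The concern.** The text promises a pre-injury measure of function, and the schedule shows none. Only EQ-5D among the questionnaires is marked at baseline, and it does not fill the gap: "The EQ-5D-3 L obtains information pertaining to the current health status of the participant and measures physical, emotional and social status". Taken after an acute fracture, a current-status quality-of-life score is neither pre-injury nor specific to the wrist.

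Two things are at stake. First, the planned baseline comparison would contain nothing on the scale that carries the primary conclusion. Second, patients differ in wrist function before injury. The trial takes all adults from 18 years, and its exclusion for earlier wrist trouble covers only symptoms or limitation linked to a previous fracture, injury or surgery in that wrist. Disability from other causes, such as arthritis, is eligible and adds spread to the 6-month PRWE. A baseline on the same scale would remove part of that spread without recruiting anyone else. A value taken before allocation cannot reliably be recovered later.

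**Working it through.** **Step 1: text against schedule.**

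| Item | Text | Table 3, baseline | Table 3, first mark |
|---|---|---|---|
| Pre-injury functional status | collected after consent, instrument not named | no row | none |
| PRWE (function, primary) | Table 2 | blank | 6 weeks |
| QuickDASH | own section | blank | 6 weeks |
| EQ-5D | own section, current health | marked | baseline |
| Radiological outcomes | own section | marked | baseline |

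Neither of the two function or disability scores is scheduled before randomisation.

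**Step 2: is there time to collect it?** The sections on trial interventions and randomisation place randomisation at surgery booking, after consent, by sealed envelope. A questionnaire can therefore be completed after consent and before the envelope is opened.

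**Step 3: the plan's own power figure.** The Sample size section gives "Recruitment of a total of 130 participants (65 in each group"), 30% loss, a difference of 10, SD 15 and 95% power. It states neither alpha nor sidedness; I assume a two-sided 5% t-test.

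- Completers: 65 × 0.7 = 45.5, taken as 45 per arm.
- Standard error: 15 × √(2/45) = 3.162. Noncentrality: 10/3.162 = 3.162, with 88 degrees of freedom and critical value 1.987.
- Power (noncentral t): 87.9%.

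The stated 95% is not reproduced on these assumptions. With all 65 per arm and no loss, power is 96.5%. With a one-sided 5% test and 45.5 per arm it is 93.5%. This is a separate matter: the calculation is for an unadjusted comparison and does not depend on a baseline PRWE. The 87.9% serves here only as the reference for step 4.

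**Step 4: what a baseline covariate could add.** If baseline PRWE correlates r with 6-month PRWE, the residual SD is 15 × √(1 − r²). The article does not give r, so every value is an assumption.

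| r | Residual SD | Standard error, 45 per arm | Power |
|---|---|---|---|
| 0 | 15.00 | 3.16 | 87.9% |
| 0.1 | 14.92 | 3.15 | 88.2% |
| 0.3 | 14.31 | 3.02 | 90.6% |

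The gain is 88.2 − 87.9 = 0.3 points at r = 0.1 and 90.6 − 87.9 = 2.7 points at r = 0.3.

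**Step 5: covariate or change score.** If the baseline SD were also 15 (an assumption), a change score would have SD 15 × √(2(1 − r)). At r = 0.3 this is 17.75 and power falls to 75.3%. At r = 0.5 the SD is 15 again, with no gain. With a weak correlation the baseline should be a covariate and should not be subtracted.

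**The case against.** **The mismatch may be only apparent.** The sentence puts pre-injury function next to demographic information, which is not in Table 3 either. That table lists intervals for outcome measures given by a blinded assessor, so it need not list every baseline item. Pre-injury function could be recorded on another form, and a condensed article may leave that form to the full protocol. This stands as far as it goes: the two places are not in strict contradiction. It still leaves the instrument unnamed and the PRWE without a baseline in the only schedule shown.

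**The gain may be negligible.** Patients with ongoing trouble from earlier wrist trauma or surgery are excluded, so many pre-injury scores may lie near zero and say little about the 6-month score. Recall error weakens the correlation further. This also stands. Recall error does not bias the plate comparison, however, if the score is completed before allocation is known.

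**Stronger readings that the article does not support.**

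- A reader might infer that the 6-month comparison is biased or invalid without a baseline. Randomisation makes it valid, and neither the sample size nor the planned analysis relies on adjustment.
- A reader might infer that change measured from 6 weeks would remove a plate effect already present then. Paired tests within a group do not estimate a plate effect, unpaired tests at 6 months compare levels, and no endpoint of change from 6 weeks is named.
- A reader might infer that adjustment restores the stated 95% power. Power would reach 95.1% at r = 0.5, but nothing in the article supports that correlation between recalled pre-injury and 6-month scores. The shortfall was not caused by the missing baseline.

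**Conclusion.** The point holds as an inexpensive improvement and does not show an error in the primary comparison. On the schedule as printed, the primary scale has no value before randomisation, and the promised functional status is not tied to any instrument. The cost is some precision and the ability to show balance on the PRWE.

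The precision at stake is about 0.3 points of power at r = 0.1 and 2.7 points at r = 0.3. These figures rest on a two-sided 5% test, 45 completers per arm, the stated difference of 10 and SD 15, and on correlations that are assumed. Floor effects would put the gain at the low end.

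**What to change.** 1. Under Outcome measures, name the instrument: recalled pre-injury status on the PRWE, with the recall period stated.
2. Mark PRWE in the baseline column of Table 3, with a note that it is completed after consent and before the randomisation envelope is opened.
3. Under Statistical analysis, enter the baseline PRWE as a covariate in the model for the 6-month contrast between plates, and state that it is not used to form a change score.

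If some other instrument was meant, name it and show when it is collected.

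The cost is one 15-item questionnaire at a contact where baseline data are already taken, a few minutes of the patient's time, and one model term. Recall error and floor effects may keep the benefit small.

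The stated power should be dealt with separately and should not be treated as repaired by this change.

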### Patient rated wrist evaluation (PRWE)

The PRWE is a 15-item questionnaire designed to measure wrist pain and disability in activities of daily living. The PRWE allows patients to rate their levels of wrist pain and disability from 0 to 10, (0 = no difficulty, 10 = unable to do) and consists of 2 subscales:

1) PAIN subscale – 5 items.

2) FUNCTION subscale - 10 items (specific and usual activities).

In addition to the individual subscale scores, a total score can be computed on a scale of 100 (0 = no disability), where pain and function problems are weighted equally.

The PRWE is a standardized outcome tool that is easy to administer and score, and complements traditional impairment and radiographic measures. The PRWE has been used to assess wrist-related pain and disability in various populations and its reliability, validity, and responsiveness have been tested and reported in published studies [17].

The secondary outcome measures in this trial are the:

### Adverse events

The following adverse events will be recorded: significant reduction in movement (6 weeks or greater), high levels of reported pain (2 weeks or greater), significant reduction in function (6 weeks or greater), non-union, malunion, infection, chronic regional pain syndrome, implant failure (eg implant breakage, screw migration, loosening), fracture fixation failure (implant failing to maintain fracture fixation), tendon irritation (3 months or greater), tendon rupture, nerve injury, excessive scarring or hypersensitivity (6 weeks or greater).

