## Background

Distal radius fractures are the most common type of all fractures seen in the emergency department and constitute 10% to 25% of all extremity fractures [1,2]. The incidence of distal radius fractures continues to rise as the population in industrialised countries grows in line with an increase in age and life expectancies [3,4]. The occurrence of distal radius fractures peaks within two different age groups: high energy trauma, typically in males aged 5–24 years, or low-energy injuries commonly seen in the elderly female population aged 65 years and older [5].

The treatment of distal radius fractures has developed greatly over recent years with a move towards treating these fractures by means of internal fixation. Although closed reduction and casting remain viable options for some non-displaced simple fractures of the distal radius, the role of ORIF continues to grow due to its ability to more reliably restore wrist anatomy, minimize immobilization and establish acceptable clinical outcomes [4]. Numerous methods of surgical stabilisation exist including: manipulation with Kirschner wires (k-wires), external fixators, dorsal and volar plating and fragment specific fixation. All have been found to be successful in maintaining correction of the reduced fracture however volar plating has more recently become the favourable choice for managing distal radius fractures especially in more complex fracture patterns and/or osteoporotic bone [6-8]. The advent of variable angle volar plating systems has also allowed cases with increasing comminution and displacement, poor bone quality, and dorsally angulated fractures, to be fixed with less tendon irritation and the reduced need for hardware removal [8,9]. In addition, volar plating allows restoration of anatomy, stable fixation, reduced periods of immobilisation and earlier return to function [6,8]. As the popularity of volar plating has increased so has the number and type of volar plating systems available to orthopaedic surgeons. Differences range from the plate design (i.e. shape and contour), material, type, locking screw mechanism and number of screws used. The general benefits of variable angle plating systems have been reported to include [8]:

•Flexible deployment with respect to variations in radial size;

•Accommodation of proximal/distal variation in volar fracture lines;

•Accommodation of medial and lateral variation in fracture lines;

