Park et al. investigated the clinical outcomes of a consecutive cohort of 20 patients undergoing ORIF of their distal radius fractures using the Medartis Aptus Volar Plate up to a one year period [4]. They found that all fractures healed in every case by 12 weeks post-operation with no loss of reduction in 19 cases (of 20 patients). Range of movement, grip strength and Disability of the Arm, Shoulder and Hand (DASH) scores were all within acceptable ranges.

Previous studies have investigated the clinical and radiological outcomes of volar plating systems in cohort series designs [9,13,14]. Osada et al. found in their series of 49 fractures in 49 patients fixed with volar plates, good radiological results, good to excellent Gartland and Werley scores, low DASH scores, a high degree of patient satisfaction and no record of complications except plate removal [13]. A total of three plates were removed between six and 10 months postoperatively. Two plates were removed due to patient request and the other was removed because the distal locking pins appeared to be intra-articular on the computed tomography scan [9]. Sanchez-Crespo retrospectively reviewed 145 patients (fixed with either a Medartis Aptus Volar 2.5 mm Plate or Synthes 2.4mmLCP distal radius plate) and analysed results of 95 of these patients [14]. They found good mean functional scores using the PRWE (mean 13; range 0–64) however 8% of patients presented with a complication (e.g. chronic pain, malunion, tendon tears, carpal tunnel syndrome, or requiring hardware removal).

Titanium and stainless steel volar plating systems for distal radius fractures are both readily available and in common use in orthopaedic surgery. Titanium implants have been reported to have benefits including reduced implant stiffness, increased biocompatibility and diminished stress shielding [15]. However tenosynovitis and extensor tendon ruptures have been reported in the use of low profile titanium plates used for dorsal fixation of distal radius fractures [16]. Conversely, stainless steel plates have been thought to have less tendon irritation and adhesions when used in wrist surgery [16].

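### The adverse-event list does not name hardware removal, although the Background counts plate removal as a complication

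*Protocol article*

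**What the plan says.** The Adverse events section opens with "The following adverse events will be recorded: significant reduction in movement (6 weeks or greater") and continues through 13 items. The items on hardware are "implant failure (eg implant breakage, screw migration, loosening), fracture fixation failure (implant failing to maintain fracture fixation"). Removal of a plate or screws is not an item. Nor is it named in Table 2, Table 3 or the Statistical analysis section.

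The Background treats removal differently, in three places:

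- One 49-patient volar plate series is summarised as having "no record of complications except plate removal".
- In a retrospective series with 95 patients analysed, "8% of patients presented with a complication (e.g. chronic pain, malunion, tendon tears, carpal tunnel syndrome, or requiring hardware removal").
- Variable angle volar plating is credited with "less tendon irritation and the reduced need for hardware removal".

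The Abstract gives uncertainty about which plating system has the lowest complication rate as a reason for the trial. The Statistical analysis section says "The complication rates will be reported in terms of frequency" and plans a between-arm comparison, with Pearson chi-square as the example.

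**The concern.** The article motivates the trial partly by complication rates and counts removal among the complications of earlier series. It then gives an explicit list that leaves removal out. If the list is followed as written, two things are lost:

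- **Removals without a listed cause.** These leave no trace in either arm.
- **The fact and date of any removal.** Removal ends exposure to the plate. Tendon events after it, and hardware findings on the 24-month X-ray, are easier to interpret when the date is known.

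**Working it through.** The plan gives no complication rate or removal rate, so there is no figure of its own to reproduce. The check is a comparison of texts, followed by a calculation for scale.

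**1. Are the cited removals on the list?** The Background says "A total of three plates were removed between six and 10 months postoperatively" and gives the reasons.

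| Reason in the cited series | Number | Matching item on the list |
|---|---|---|
| Patient request | 2 | None |
| Distal pins appearing intra-articular on CT | 1 | None named; not clearly breakage, migration, loosening or loss of fixation, though it might be noted as a hardware complication on imaging |

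**2. Which removals would leave a trace?** Pain, tendon irritation, tendon rupture, infection, nerve injury, implant failure and fixation failure are all listed. A removal for one of these enters the record under its cause, but not as a removal.

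**3. Would imaging fill the gap?** In Table 3, radiological assessment is fixed at baseline, 2 weeks, 6 weeks and 2 years. At 3, 6 and 12 months it is done only if care requires it. The cited removals took place at six to 10 months, inside that gap. A 24-month film could show that a plate is gone, but not when or why.

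**4. Scale.** Inputs: 3 removals, 2 of them by request, in 49 patients (Background); 65 per arm and 30% loss (Sample size).

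- All removals: 3/49 = 6.1%, Clopper-Pearson 95% CI 1.3% to 16.9%.
- Expected per arm: 65 × 3/49 = 3.98, about 4. Over the interval: 65 × 0.0128 = 0.8 to 65 × 0.1687 = 11.0.
- Not by request: 1/49 = 2.0%; 65 × 1/49 = 1.3 per arm.
- Among those retained: 65 × 0.7 = 45.5 per arm, giving 45.5 × 3/49 = 2.8 removals, of which 45.5 × 1/49 = 0.9 not by request.

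**5. Could a test of removal be informative?** Take illustrative rates of 6% and 12%, a two-sided 5% level and the normal approximation: power = Φ{[|p₁−p₂| − 1.96√(2p̄(1−p̄)/n)] / √[(p₁q₁+p₂q₂)/n]}. With n = 65 this is Φ{(0.06 − 1.96 × 0.0502)/0.0499} = 0.22. With n = 45.5 it is 0.17. Removal is therefore an item to describe by arm, not one on which to base a test.

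**The case against.** The strongest reply is that little is really lost. Most symptomatic reasons for taking a plate out are already listed, and the examples under implant failure are open-ended. Imaging has its own checklist and an added 24-month film. The adverse-event checklist is not shown and may hold more than the article prints. What clearly escapes is mainly removal at patient request, and whether that is an adverse event at all is a matter of definition.

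Much of this stands. It limits the point to removals with no listed cause and to the fact and date of every removal. It does not remove the point: the article prints an explicit list without deferring to a fuller one, and that list does not match the Background's use of the word complication.

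A reader might infer more than the documents support:

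- **That the complication comparison would miss removals altogether.** It would not; many would appear under their cause.
- **That the trial's rates could not be set against the cited 8%.** No such comparison is planned. The examples behind the 8% have no stated removal share, and the trial's list already differs from them in other items.
- **That the Background counts reoperation or revision as a complication.** It names only plate or hardware removal.
- **That removal is among the most plate-specific events.** That is opinion; the text supports only that removal is treated as a plate complication.
- **That every removal belongs in the combined rate.** This would mix in preference-driven procedures and could count one episode twice, for example tendon irritation and the removal done for it.

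**Conclusion.** The point holds in a limited form. The stated list does not name hardware removal, while the Background treats it as a complication. Followed as written, the list leaves unrecorded the fact and date of removal, and any removal without a listed cause (patient request, possibly intra-articular screws).

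The likely number is small: about 4 per arm in all, and 1 to 2 per arm not by request. This assumes that one small uncontrolled series carries over to this trial. The article does not say that the series used either trial plate. It also assumes that the three removals belong to the 49-patient series, as the paragraph reads, although the reference numbers attached to those sentences differ. The interval is wide, and the unseen checklist may already include removal.

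This is a minor but worthwhile correction to a secondary outcome. It does not touch the PRWE analysis, the sample size or any stated figure.

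**What to change.** Add to the Adverse events list and to the study checklist: *hardware removal (partial or complete), with date and reason*. Record it at each complications visit in Table 3, to 24 months.

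Report it by arm as a separate item in two rows: hardware- or symptom-related removal, and removal at patient request alone. In any patient-level complication rate, count a patient with hardware- or symptom-related removal once, including when the cause is also listed, and leave out request-only removals.

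The cost is one checklist line, a small addition to the results table and a judgement of the reason for each removal. That judgement is the one real downside. The change concerns recording and reporting only.
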